### Sample size

In our pilot study [34], we found a partial eta square of 0.088 for the repeated-measures ANOVA examining the effect of mindfulness on Go/No-Go performance as a function of working memory index. Based on an alpha of 0.05, a total sample size of 103 would be needed to yield an estimated power greater than 0.80. Given the attrition observed in our pilot study (~ 20%), the 12-month duration of the proposed intervention, and multiple assessment sessions, we will recruit at least 130 participants to account for a potential 25% drop-out rate. Power analysis for the imaging data was based on the parameter estimates in the Kilpatrick study [52] examining the impact of mindfulness training on functional connectivity of resting-state networks. The resulting effect sizes were *d* = 1.29 and *d* = 0.99 for auditory/salience regions To be conservative, we used the effect size of *d* = 0.99. To detect an effect of this size with 90% power, we would need 23 subjects per group for a total of 46 people. A study by Kilpatrick and colleagues [52] compared their mindfulness intervention against a wait-list control group. It is likely that the parameter estimates of their study include variance that may be accounted for by non-specific factors. In the present study, our mindfulness training group will be compared with an active control group that will control for many of the non-specific factors. Thus, assuming an effect size of *d* = 0.76, we plan on collecting MRI data on 75 participants to yield an estimated power greater than 0.90.

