### Study procedures

Participants are being drawn from the greater central Ohio area. Recruitment for the study started in August 2018 and is currently ongoing. We are implementing a multi-medium recruitment strategy, advertising for the study using both printed and online communications, in-person recruitment, community outreach, and other opportunities aimed at our targeted demographic. Table 1 provides a list of our primary recruitment sources for the study. Participants interested in the study will either complete a phone screen or an online survey that is designed to collect basic demographic information, current medications, and history of physical as well as psychological health. Participants who meet basic inclusionary criteria are then invited to the Clinical Neuroscience Laboratory at The Ohio State University to complete an in-person screening session. Those meeting the study criteria as described above are invited for additional behavioral and imaging-based assessments. Table 2 lists the measures administered at pre-training, post-training, and at 6-month and 12-month follow-up sessions. Participants are also given a Qualtrics link with the following survey measures at baseline, pre-training, post-training, and the two follow-up sessions: the Mindful Attention Awareness Scale [53], the Difficulties in Emotion Regulation Scale [54], the Perceived Stress Scale [55], the World Health Organization Quality of Life – BREF [56], the Beck Anxiety Inventory [57], the Five Facet Mindfulness Questionnaire [58], the Coronavirus Anxiety Scale [59], Psychological Stress Associated with the COVID-19 Crisis [60], and the Everyday Discrimination Scale [61].

**Table 1 Tab1:** List of primary recruitment sources being employed for the study

Category	Recruitment Strategy
**Printed Materials**	Flyers were displayed in recreational centers, community centers, libraries, cafes, barber shops, and churches throughout the central Ohio area
	Advertisements were displayed on Campus Area Bus Service buses at The Ohio State University
	Post cards were distributed to households in the central Ohio area
**Online Recruitment**	Research Match (an online recruitment tool with a database of participants.)
	Study Search (a database of active studies at The Ohio State University)
	Media advertisements (Facebook, Columbus Dispatch, Ohio State University’s OnCampus newspapers)
**Radio Advertisement**	Radio Stations aired an advertisement for the study (106.7 The Beat)

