After preprocessing of behavioral and neuroimaging data, all data will first be tested for normality, outliers, and errors. We will then compute summary statistics and compare groups’ baseline demographic and clinical characteristics; although randomization should balance the groups with respect to these characteristics, with a finite sample size, there may be some residual imbalance. Particular attention will be paid to characteristics that may be associated with outcomes (e.g., education, depression scores) as chance imbalance in these characteristics may confound the intervention effects. All statistical analyses conducted as part of the trial will be intent-to-treat. The primary outcome variables for this study are indices of attentional control and mind-wandering. To examine the immediate effects of mindfulness training, we will use a linear mixed model to account for the within-subject correlation arising from measuring each subject at two timepoints. Group (MBSR, LifeEd), Time (pre and post-training), and the Group X Time interaction will be defined as fixed effects, with covariates, when applicable (e.g., those identified as randomly differing between groups) included as fixed effects. Each participant’s intercept will be included as a random effect. To determine the maintenance effects of mindfulness meditation, we will construct a separate mixed linear model examining the long-term efficacy of mindfulness meditation with Time (pre-training, 6-month follow-up, and 12-month follow-up), Group (MBSR, LifeEd), and the Group X Time interaction effects. Secondary factors of functional connectivity, fluid and everyday cognition, emotion dysregulation and inflammation will also be examined by constructing linear mixed models.

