## Discussion

This ongoing Phase I/II randomized controlled trial (HealthyAgers) is designed to evaluate the efficacy of mindfulness-based stress reduction, compared to a carefully designed, active control group (Lifestyle Education), in improving attentional control, reducing mind-wandering, and strengthening the functional connections subserving attentional processing in older adults. With the provision of quarterly booster sessions and the availability of a web-based and mobile application designed to promote adherence to mindfulness practices, this study will also be able to determine the longitudinal effect of engagement in mindfulness practices for maintenance of attentional benefits. Additionally, with secondary assessments involving global and everyday measures of cognition, emotion regulation, and systemic markers of inflammation, results of this study will also add to our understanding of whether mindfulness training has the potential to improve cognitive and affective health of older adults. This systematically designed trial of mindfulness meditation with its inclusion of an active control group, assessment of theoretically-driven behavioral and neural metrics of attentional control, and longitudinal follow-up will make a significant and nuanced contribution to our understanding of whether and how engagement in mindfulness meditation promotes healthy aging.

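### The follow-up model meant to show maintenance leaves out the post-training visit, so it can show long-term efficacy versus baseline but cannot test whether the post-training gain is kept

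*Protocol article*

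**What the plan says.** The section Data management and analysis of the Protocol article sets out two models for the primary outcomes.

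- **Immediate effect.** "Group (MBSR, LifeEd), Time (pre and post-training), and the Group X Time interaction will be defined as fixed effects". The description of this two-visit model ends by saying that each participant's "intercept will be included as a random effect".
- **Follow-up.** "To determine the maintenance effects of mindfulness meditation, we will construct a separate mixed linear model examining the long-term efficacy of mindfulness meditation". This second model is specified "with Time (pre-training, 6-month follow-up, and 12-month follow-up), Group (MBSR, LifeEd), and the Group X Time interaction effects". No random effects or residual covariance are given for it.

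The post-training data exist: "Table 2 lists the measures administered at pre-training, post-training, and at 6-month and 12-month follow-up sessions". In that table, both primary tasks are given at all four of these time points, while neuroimaging and blood are taken at pre-training, post-training and 12 months only. The Discussion presents maintenance as a question the trial will answer, saying that it will be able to "determine the longitudinal effect of engagement in mindfulness practices for maintenance of attentional benefits". The Sample size section allows for loss, with recruitment set "to account for a potential 25% drop-out rate".

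**The concern.** Maintaining a benefit means that what was gained by the end of the programme is still there later, so the comparison runs from post-training to follow-up. Post-training sits in one planned model and the follow-up visits in another, so no planned model contains both. As written, the trial would report an effect at post-training and effects at 6 and 12 months, with no interval or test for the change between them.

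The second issue is missing data. A participant who attends post-training and is then lost contributes only a baseline value to the follow-up model, although a later score was observed. A likelihood model that includes this score stays valid when drop-out depends on it. A model that omits the score generally does not.

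**Working it through.** The plan gives no figure for the follow-up model, so there is none to reproduce. Correlations and drop-out mechanisms below are assumptions, because the documents state neither. The 25% loss is the Sample size section's allowance.

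**1. What the three-visit model can estimate.** Let δ(t) be the arm difference in change from pre-training at visit t. Retention is R = δ(12) − δ(post).

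- Gain kept: δ = 0.3, 0.3, 0.3 SD at post-training, 6 and 12 months; R = 0.3 − 0.3 = 0.
- Gain half lost: δ = 0.6, 0.3, 0.3 SD; R = 0.3 − 0.6 = −0.3 SD.

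The three-visit model contains only δ(6) and δ(12), which are 0.3 and 0.3 in both cases. Its expected results are therefore identical, and R is not a parameter of it. Subtracting the estimates of the two separate models gives a point value for R. Neither fit supplies the covariance between the two estimates, so there is no standard error.

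**2. Drop-out, large-sample calculation.** Inputs: true 12-month effect 0.30 SD; 25% loss per arm, all between post-training and 6 months; correlations pre–post 0.70, pre–12 months 0.50, post–12 months 0.65; logit of drop-out linear in the pre-to-post change, slope ±1 per SD. The likelihood estimate of each arm's 12-month mean is the completers' mean plus b × (mean of all participants − mean of completers) on the earlier visits in the model, where b is the regression slope among completers.

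| Drop-out depends on early change | Without post | With post | Bias without post |
|---|---|---|---|
| MBSR only, slope −1 | 0.37 | 0.30 | 0.37 − 0.30 = +0.07 |
| MBSR only, slope +1 | 0.23 | 0.30 | 0.23 − 0.30 = −0.07 |
| Same slope in both arms | 0.30 | 0.30 | 0 |

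Two variations on the first row shrink the bias. If half of that loss falls after the 6-month visit (6-month correlations assumed 0.60 with pre, 0.70 with post and 0.70 with 12 months), the estimate is about 0.35. If half of all drop-out occurs before post-training, it is 0.33 to 0.34.

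**3. Drop-out, simulation at trial size.** Inputs: N = 130, 1:1; 400 trials per scenario; about 25–30% lost after post-training; true 12-month effect 0.50 SD; unstructured covariance in both models. The true correlations are either equal at 0.6 or decaying by a factor of 0.75 per 6 months. Where drop-out is not random, it depends on the post-training score with logit slope 1.2. Monte Carlo error is about 0.19/√400 ≈ 0.01.

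| Drop-out | Pre, 6, 12 months (equal / decaying) | Pre, post, 6, 12 months (equal / decaying) |
|---|---|---|
| Completely random | 0.49 / 0.50 | 0.49 / 0.50 |
| On post score, same in both arms | 0.48 / 0.50 | 0.50 / 0.51 |
| On post score, MBSR only | 0.57 / 0.54 | 0.51 / 0.51 |
| On post score, opposite directions by arm | 0.61 / 0.56 | 0.49 / 0.50 |

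The largest bias is 0.61 − 0.50 = +0.11 SD. Precision barely differs: the empirical standard error is 0.17 to 0.20 for both models.

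**The case against.** The strongest defence is that the same sentence also calls the purpose long-term efficacy. The arm difference in change from baseline at 6 and 12 months answers that validly, and whether a benefit over control is still present at 12 months is a reasonable everyday sense of maintenance. This stands: the model is not useless, and what is missing is specifically a retention contrast.

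The drop-out point can also be resisted. The 25% is an overall allowance. People lost during the eight-week programme have no post-training score to add, the planned model does use 6-month data, and the section on adherence promises every attempt to assess those who stop the intervention. This also stands, and it makes the bias conditional. That the post-training score explains who leaves is an assumption, not something the documents show.

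Two stronger readings are tempting, and the documents support neither.

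- **Equal correlation.** A reader might infer that the follow-up model carries over a random intercept and so forces equal correlation across visits, giving false standard errors. The random intercept is stated for the two-visit model, where there is only one correlation to fit. The covariance of the separate model is unstated and may be left to the full protocol or SAP. Even if it were carried over, with assumed correlations of 0.70/0.55/0.70 a nominal 5% test would run at about 8.4% for the 12-month contrast but 3.4% for the 6-month one. The 12-month figure alone would mislead.
- **Degrees of freedom.** A reader might blame the omission for an interaction test on 2 degrees of freedom without direction. A three-level Time factor gives 2, and adding post-training would give 3, so the omission is not the cause.

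**Conclusion.** The point holds in a limited form. The follow-up model cannot test whether the post-training gain is kept, although the plan names maintenance as its purpose. This follows from the listed visits and needs no assumption. The model does validly address efficacy at 6 and 12 months relative to baseline, and the immediate-effect analysis is untouched.

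The drop-out consequence is conditional. Under the assumed mechanisms, the bias in the 12-month effect runs from about nil to about 0.1 SD, in either direction. It is material only when drop-out depends on early response differently in the two arms. These are illustrations rather than bounds, since stronger dependence would give more. Leaving out the visit saves nothing in precision, so there is no statistical reason to accept the exposure.

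**What to change.** Replace the two models with one likelihood-based mixed model per outcome that uses every collected visit: pre, post, 6 and 12 months for the behavioral outcomes, and pre, post and 12 months for MRI and blood. Pre-specify:

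- the between-arm contrast for change from pre-training at each later visit, which covers the immediate and long-term effects;
- the between-arm contrast for change from post-training to 12 months (and to 6 months where collected) as the maintenance test, with its interval.

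With more than two visits, name a covariance that does not force equal correlation, such as unstructured. This completes the fix and does not correct an error in the text.

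The cost is a change of wording and a few more covariance parameters: an unstructured matrix has 4 × 5 / 2 = 10 for four visits, against 3 × 4 / 2 = 6 for three. No new data are needed.

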### Adverse event reporting

Adverse events are being graded using the common grading scale proposed by the National Institutes of Health: (a) No adverse event (event is within normal limits or not clinically significant), (b) Mild adverse event that does not require treatment, (c) Moderate adverse event that was resolved with treatment, (d) Severe adverse event that resulted in an inability to carry on normal activities and required professional medical attention, (e) Life threatening or disabling adverse event, and (f) Fatal adverse event. All study personnel are trained to monitor for adverse events, and, upon notification of an adverse event, the study PI ([name]) determines the relationship of the adverse event(s) to the intervention as unrelated, possibly related, probably related, or definitely related using the standard criteria for clinical trials. For every adverse event, a written report of the adverse event is submitted to the local IRB within 10 days of the occurrence of the event. The IRB along with the PI then determines the relationship of these events to the study protocol and determines whether the adverse event was related the design of the study. If the adverse event is not related to the design of the study or is a mild adverse event related to the design of the study, these adverse events are documented along with any changes in the protocol that will be implemented to prevent future occurrences. Additionally, the event is reported to the NIH and the Data and Safety Monitor appointed for this study at the bi-annual meeting. If the adverse event is reported to be related to the study and is classified as a moderate adverse event and above, in addition to submitting a report to the IRB, a full report will be prepared and submitted within 10 days of the adverse event to the Data and Safety Monitor. This report will include a full, detailed description of the event as well as the response of the research team. If two participants experience the same adverse event, we will immediately stop recruitment for the study, prepare a report for the IRB and the Data and Safety Monitor, and incorporate any revisions to the study protocol suggested by the monitor. Additionally, annual reports will also be submitted to the IRB indicating the progress of the study, including information on enrollments, withdrawals and completions, and the occurrence of adverse events.

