### Randomization

Eligible and consenting participants will be randomized after completing baseline assessments to one of two groups: MBSR or LifeEd. A random permuted-block design (blocks of size 2 and 4) will be used, and the randomization with an allocation ration of 1:1 will be stratified by sex assigned at birth (male, female), cognitive status (cognitively normal, MCI), and MRI eligibility (eligible, not eligible) to ensure balance across these important factors. The biostatistician on the team, [name], prepared and maintains the randomization sequence for the eight strata. The project coordinator has been given concealed envelopes and only after a participant completes all pre-assessment sessions and is deemed eligible for the study does the project coordinator open the envelope from the respective stratum and assign the participant to either the MBSR or the LifeEd group. The project coordinator, the study facilitators and supervisors, and the study biostatistician will be the only members of the team who will be unblinded to group assignment. All personnel conducting assessments, behavioral or neuroimaging, will remain blind to group assignment.

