**TRAINING**	
4. Formal facilitator training	4. 25 h. of face-to-face facilitator training for MBSR and 25 h. of training control groups with MBSR instructor and PI with 22 and 12 years of experience, respectively
5. New facilitator monitoring	5. PI and MBSR consultant will provide weekly 1.5 h. group supervision + 30 min. of individual supervision

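### Severity alone never triggers a prompt report to the Data and Safety Monitor, so an isolated fatal or life-threatening event classed as unrelated waits for the bi-annual meeting

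*Protocol article*

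**What the plan says.** All the reporting rules are in the Adverse event reporting section of the protocol article. The severity scale runs from no event through mild, moderate and severe to life-threatening or disabling, and fatal.

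Relatedness is judged twice. The PI first "determines the relationship of the adverse event(s) to the intervention as unrelated, possibly related, probably related, or definitely related". A written report of every event then goes to the local IRB within 10 days of its occurrence, and the IRB and the PI together determine the relationship.

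The route to the Monitor follows from that judgement:

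- **Slow route.** "If the adverse event is not related to the design of the study or is a mild adverse event" related to the design, it is documented and "the event is reported to the NIH and the Data and Safety Monitor appointed for this study at the bi-annual meeting".
- **Prompt route.** "If the adverse event is reported to be related to the study and is classified as a moderate adverse event and above", then, besides the IRB report, "a full report will be prepared and submitted within 10 days of the adverse event to the Data and Safety Monitor".
- **Repeat-event route.** If the same event occurs in two participants, recruitment stops and a report is prepared for the IRB and the Monitor. No relatedness or grade condition is attached.

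On blinding, the Randomization section states: "The project coordinator, the study facilitators and supervisors, and the study biostatistician will be the only members of the team who will be unblinded". The PI is not named there. Table 3 (Training) says "PI and MBSR consultant will provide weekly 1.5 h. group supervision + 30 min. of individual supervision" for new facilitators, and the text on facilitation and fidelity describes the PI as training the facilitators.

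**The concern.** One reason for appointing a Data and Safety Monitor is to have someone outside the team look at serious events, including whether their attribution is credible. Under this rule, the attribution decides whether the Monitor sees a serious event promptly. The Monitor has no stated part in making it. The PI takes part in both determinations and appears to know the arm.

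The participants are aged 65 to 85 and are followed for 12 months after an eight-week programme, so serious events with no obvious link to a mindfulness or education course are foreseeable. Those are the events most easily classed as unrelated. What is at stake is the timeliness of independent safety review. The efficacy analysis is not affected.

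**Working it through.** The documents give no figure to reproduce. The check is to follow each kind of event through the rules as written.

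| Event | IRB | Data and Safety Monitor |
|---|---|---|
| Related, moderate or above | within 10 days | full report within 10 days |
| Related, mild | within 10 days | bi-annual meeting |
| Not related, mild or moderate | within 10 days | bi-annual meeting |
| Not related, severe, life-threatening or fatal; first or isolated | within 10 days | bi-annual meeting |
| Same event in a second participant, any grade or attribution | report prepared | report prepared, no number of days given |

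The fourth row is the gap. The prompt route joins two conditions, relatedness and grade, and failing the first removes the event whatever the second says. The slow route puts no ceiling on the grade of unrelated events. No sentence in the section makes an exception for the top grades.

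**Length of the delay.** The inputs are the 10-day limit (stated) and the interval between meetings (called bi-annual; taken here as twice a year, an assumption).

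- Longest wait: 365 / 2 = 182.5, about 183 days or 6 months.
- Average wait, if the event is equally likely on any day between meetings: 182.5 / 2, about 91 days.
- Comparator: 10 days for a related event of moderate grade or above.

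An event shortly before a meeting would wait very little, so the range is 0 to about 183 days.

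**Which determination controls the route.** The section uses three referents for relatedness. The PI's scale concerns the intervention, the slow route concerns the design of the study, and the prompt route concerns the study. These need not agree. An event judged possibly related to the intervention but not to the design could be read into either route. The order of steps adds to this. The joint determination by the IRB and the PI comes after an IRB report that may arrive as late as day 10, while the Monitor's report is also due within 10 days of the event. The text does not say whether the PI's first call or the joint one starts the Monitor's report.

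**Whether the PI is unblinded.** Supervisors are listed among the unblinded staff, and Table 3 makes the PI a supervisor of facilitators. Together these imply that the PI knows the arm. No passage says so directly.

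**The case against.** The strongest reply is that the plan already has two safeguards, and both stand.

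- **The IRB.** Every event, of any grade and attribution, is reported to the IRB within 10 days, and the IRB shares in the relatedness decision. A reader might infer that the Monitor is the only independent reviewer, or that the PI alone decides the route. The section supports neither reading. The IRB report does not replace the Monitor's, however, since related events of moderate grade or above go to both.
- **The repeat-event rule.** A reader might infer that a run of serious events, each called unrelated, would stay out of the Monitor's sight between meetings. For repeats of the same event that is wrong: the second occurrence leads to a Monitor report whatever the attribution. The rule does not catch a first event, a single event, or serious events that differ from one another. Nor are those events concealed; they reach the Monitor at the scheduled meeting.

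It can also be said that both programmes are group courses with light exercise or meditation, so a graded reporting scheme is a reasonable choice, and that operational details such as the handling of possibly related events may sit in a full protocol or monitoring plan that is not shown. That is fair for the details, and they are not pressed here. It does not answer the routing rule, which the article states in full and which treats an unrelated death like a mild event.

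**Conclusion.** The point holds in a limited form. As written, grade alone never brings an event to the Monitor promptly, so a first or isolated severe, life-threatening or fatal event classed as unrelated waits for the bi-annual meeting: 0 to about 6 months, against 10 days. This rests on reading bi-annual as twice a year. A reader might take it as every two years and infer a delay of up to 24 months, but nothing in the article supports that.

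Three further inferences should not be drawn.

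- That the PI is unblinded is a reasonable deduction from the supervision arrangements, but it is not a stated fact.
- No expected number of deaths can be given. The article states no mortality rate, excludes terminal illness, requires intact daily function and allows for 25% drop-out.
- The article describes no comparison of related events by arm, so a bias in such a count cannot be charged against a planned analysis.

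The delay for any one event depends on none of these. I regard this as a worthwhile, inexpensive improvement in safety oversight, with the gap partly covered by the IRB and the repeat-event rule.

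**What to change.** In the Adverse event reporting section:

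1. Send the written report already prepared for the IRB to the Data and Safety Monitor, in the same 10-day window, for every severe, life-threatening or fatal event whatever its attribution. Keep the present rule for moderate related events and the bi-annual route for the rest.
2. Use one referent for relatedness throughout, and state which determination, the PI's or the joint one, controls the route to the Monitor.

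The cost is a few sentences of wording and a few more interim reports for the Monitor to read. The IRB report is already written for every event, so no new document is needed. Design, sample size and analysis do not change.
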